### Recruitment {15}

The strategies for achieving adequate school enrolment to reach the target sample size will include contacting and presenting the study municipality authorities who are expected to help to establish contact with school authorities. Additionally, research assistants will contact directly and inform school authorities about the purpose, requirements, and duration of the study. Our research team already has good collaborative networks with municipalities and schools in Chile.

## Assignment of interventions: allocation

Randomization will be performed once all schools are recruited. Schools will be randomly assigned to either group with a 1:1 allocation by computer-generated randomization.

### Sequence generation {16a}

Randomization will be performed once all schools are recruited. Schools will be randomly assigned to either group with a 1:1 allocation by computer-generated randomization.

### Concealment mechanism {16b}

After the randomization and allocation, schools will be informed by a research assistant of the group of belonging by email and confirmed by telephone. Each school will only receive their information of allocation. Additionally, this information will not be disclosed to the assessment research team (outcome evaluators) to keep the blind to the schools’ allocation.

### Implementation {16c}

An independent statistician will perform the randomization to assign to the study arms, and this statistician will give this information to a research assistant. Later, the research assistant will inform to schools by email and confirmed by telephone.

## Assignment of interventions: Blinding

### Who will be blinded {17a}

This is a double-blinded trial, blinded to the outcome evaluators and to the data analyst. Outcome evaluators will not be informed about the group of belonging and will be instructed not to ask for the school condition to the students nor to the school authorities. A data analyst will work with the final dataset where the group condition will be masked.

### Procedure for unblinding if needed {17b}

The design is open label with only outcome assessors and data analysts being blinded so unblinding will not occur. On the other hand, due to the nature of the intervention, the participants will know the allocation of the school.

## Data collection and management

### Plans for assessment and collection of outcomes {18a}

Data will be retrieved from a written self-reported questionnaire called the European Drug Addiction Prevention Trial Questionnaire [EU-Dap], and then the collected information will be transferred to an electronic database by trained research assistants.

The EU-Dap is a questionnaire aiming to screen substance use and to assess risk and protective factors among adolescents. It has 45 multi-item questions and focuses especially on tobacco, alcohol, and marijuana use. The EU-Dap instrument was developed by the research team of the Unplugged program in Europe. It was used to evaluate the Unplugged trial project, which took place between 2003 and 2005 in seven countries in Europe. In the Chilean validation primary analysis, all subscales had acceptable internal reliability (omega > 0.65). The original form of the questionnaire can be found at httpp:www.eudap.net.

### Plans to promote participant retention and complete follow-up {18b}

The schools, students, and their families will receive extensive information about the study setup and requirements during the recruitment. This information will include and stress the importance of completion of follow-up. From the start of the implementation of the assessments and the lessons of YSLQQ, students will be reminded of the value of their active participation during the whole project. Throughout the follow-up period, the researchers will check responses and, if necessary, contact schools and participants for completion of their follow-up.

### Data management {19}

After the participants have completed the questionnaires, the data will be entered into a secure platform without identifying information (each participant will be assigned an encrypted ID number). The original copies of the instruments will be filed and stored, under lock and key, in a self-storage, along with the list linking the participants’ names and ID numbers. Only the Principal Investigator, research assistants in charge of data entry, and the statistician will have access to the database. All people with access to the dataset will need to sign a Confidential Agreement to assure its commitment to not revealing identifying information.

### Confidentiality {27}

Research data will be stored using a study identification code for each participant. The key to the identification code list will only be available to the research team mentioned above and will be documented and safeguarded according to research guidelines after completion of the study. No participant identification details will be reported in publications or in any report of the study.

### Plans for collection, laboratory evaluation, and storage of biological specimens for genetic or molecular analysis in this trial/future use {33}

Not applicable. No biological specimens will be collected in this trial.

## Statistical methods

### Statistical methods for primary and secondary outcomes {20a}

General school features (size, number of teachers, etc.) will be used to compare participating schools with the ones that were invited but did not participate. Additionally, descriptive statistics will be used to compare the two arms at baseline.

Primary and secondary analysis will be conducted on an intention-to-treat basis. Odds ratios (OR) and their corresponding confidence intervals (95%CI) will be calculated as the measure of association between experimental condition (Intervention arm) and behavioral outcome, controlling for baseline outcome variable scores. Secondary analysis will be conducted considering adjustment for variables with marked imbalance at baseline. Additionally, secondary analyses will be made using the secondary outcomes and analyzed with the same approach. To take into account the hierarchical structure of the data and the cluster effect, a multilevel modeling approach will be followed in the analysis of the data. Data will be analyzed with Stata 17.0.

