### Sample size {14}

Assuming alpha 0.05 (two-sided), power 0.80, with a prevalence of regular alcohol use in the control arm of 4.18% (data available from a secondary analysis of Fourth National Survey of Violence in School Context 2014, which included this information for 7th and 8th graders), and assuming an Absolute Risk Reduction (ARR) of 2% in favor of the intervention group (38), 30 students per class, and Intraclass Correlation (ICC) of 0.02 (54), the estimated sample size is 4200 students per arm, corresponding to 35 schools in the intervention and 35 schools in the control group. Considering a potential refusal to participate of 40%, 120 schools fulfilling the inclusion criteria will be invited to participate. We used the “clustersampsi” command in Stata Software estimating the number of clusters and students in two arms, using the following command:

Clustersampsi, binomial samplesize p1 (X1) p2 (X2) m(y) rho(R)

where X1 = prevalence of regular alcohol use in arm 1, X2 = prevalence of regular alcohol use in arm 2, Y = number of children per school on average, and R = intracluster correlation. Finally, the two arms will be balanced to school size.

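### Naming the school's baseline prevalence beside the student's own baseline value could sharpen the primary comparison, though the planned analysis is valid without it

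*Protocol article*

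**What the plan says.** Under Statistical methods for primary and secondary outcomes {20a}, the effect measure is an odds ratio with a 95% confidence interval, estimated "controlling for baseline outcome variable scores". A multilevel model accounts for clustering. Adjustment for other variables is a secondary analysis, triggered by marked imbalance at baseline. Secondary outcomes are analysed in the same way. The section does not say whether the baseline score enters at student level, at school level or both, and it names no school-level baseline covariate.

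Under Sequence generation {16a}, schools are the randomised units, 1:1. Under Sample size {14}, the calculation uses "Intraclass Correlation (ICC) of 0.02 (54), the estimated sample size is 4200 students per arm", that is, 35 schools per arm. The cluster is the school: "Y = number of children per school on average". No allowance for baseline adjustment is made there.

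**The concern.** When schools are randomised, the precision of the arm comparison depends heavily on how much schools differ from one another. A student-level baseline covariate with a single coefficient takes that coefficient mostly from the within-school association, because nearly all the information on it lies within schools. If schools with much drinking at baseline tend to stay that way more strongly than individual students do, one coefficient under-corrects at school level. Some between-school variance that the baseline survey could explain then stays in the error term.

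At stake is the width of the interval for the primary odds ratio, and whether a chance difference between arms in school-level drinking is handled inside the primary model by a rule fixed in advance. Extra precision would be welcome. The Discussion itself foresees that the pandemic may have lowered prevalence and that enough schools may be hard to recruit.

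**Working it through.** **Inputs from Sample size {14}.** Two-sided alpha 0.05, power 0.80; control prevalence 4.18%; absolute reduction 2 points, so 2.18% under intervention; ICC 0.02; 30 students per class; 4200 students and 35 schools per arm, so 4200/35 = 120 students per school.

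**Step 1: reproduce the plan's figure.** Two proportions, pooled variance, no continuity correction: 1208 students per arm. Design effect 1 + (120 - 1) x 0.02 = 3.38. Then 1208 x 3.38 = 4083, and 4083/120 = 34.03, rounded up to 35 schools, or 4200 students. The stated size reproduces. Power at 4200 per arm is 0.811 with no baseline adjustment.

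**Step 2: between-school share before adjustment.** ICC / [ICC + (1 - ICC)/m] = 0.02 / (0.02 + 0.98/120) = 0.02/0.02817 = 71%. With 90 or 72 analysed students per school it is 65% or 60%.

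**Step 3: effect of each baseline term (linear approximation).** Let rw be the within-school student correlation between baseline and follow-up, and rc the correlation of true school levels. Neither is in the document, so both are assumptions. Take the ICC as equal at both times. The correlation of observed school means is r = 0.71 rc + 0.29 rw. Relative to no adjustment, the variance of the effect is multiplied by:

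- own baseline only: 1 + rw² - 2 rw r
- own baseline plus school mean: 1 - r²

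The difference is (r - rw)² = [0.71 (rc - rw)]². The school term's gain therefore depends on the gap between the two correlations and vanishes when they are equal.

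At rw = 0.3:

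| rc | own only | both | further cut | power, own only | power, both |
|---|---|---|---|---|---|
| 0.4 | 0.867 | 0.862 | 0.6% | 0.863 | 0.865 |
| 0.6 | 0.782 | 0.737 | 5.8% | 0.895 | 0.912 |
| 0.7 | 0.740 | 0.659 | 10.9% | 0.911 | 0.939 |
| 0.8 | 0.697 | 0.571 | 18.1% | 0.926 | 0.964 |
| 0.9 | 0.654 | 0.473 | 27.7% | 0.940 | 0.985 |

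Example, rc = 0.6: r = 0.71 x 0.6 + 0.29 x 0.3 = 0.513; own only 1 + 0.09 - 0.6 x 0.513 = 0.782; both 1 - 0.513² = 0.737; 0.737/0.782 = 0.942. Among settings with rc at or above rw, the largest cut in the grid run was 32.5%, at rw 0.2 and rc 0.9.

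**Step 4: check with binary outcomes.** Both simulations use 35 + 35 schools of 120, with 4.18% against 2.18%.

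- *Random-intercept logistic model, 300 trials per setting.* The median standard error of the log odds ratio, without and then with the school term, went from 0.2140 to 0.2128 (school-level correlation 0.5), 0.2078 to 0.2015 (0.7) and 0.1941 to 0.1758 (0.9), all with student-level phi about 0.25. The squared ratios are 0.99, 0.94 and 0.82. At correlation 0.7 with phi 0.14, 0.2089 became 0.1969, a ratio of 0.89.
- *School-summary analysis of the risk difference, 1500 trials per setting.* Variance ratios were 1.00-1.02 (rc 0.3), 0.93-0.95 (0.6), 0.82-0.90 (0.8) and 0.75-0.79 (0.9), with within-school phi between about 0.17 and 0.34. In the one null setting run (rc 0.8), type I error was 0.049 with no adjustment, 0.047 with own baseline and 0.048 with the school term.

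**The case against.** The strongest reply is that {20a} is one paragraph in a condensed article. It does not say that only the student's own answer enters, and the exact form of the covariates may be settled in a fuller analysis plan. That stands as far as it goes. A reader might infer that the plan rules the school's prevalence out, but the text leaves the level open. What remains is that the section does name the primary covariate, names no school-level counterpart, and sends further adjustment to an imbalance-triggered secondary analysis. A plan that followed it as written would have no school term.

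Second, nothing is invalid. Baseline adjustment in a multilevel model is a standard analysis of a cluster trial, and the sample size carries the full ICC with no credit for adjustment. This stands fully. A reader might infer bias or a loss of the promised power, and neither follows.

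Third, the student's own baseline already does much of the work. In the linear formulas with rw = 0.25, it alone removes about 15%, 22% and 29% of the variance at rc 0.5, 0.7 and 0.9, against 18%, 32% and 51% with both terms. So about 83%, 69% and 58% of the removable variance is already gone. This too stands. The 71% describes the situation before any adjustment. It is tempting to read it as the amount the school term would recover, and it is not.

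**Conclusion.** The point holds as an improvement in efficiency and prespecification. Beyond adjustment for the student's own baseline, the school term would reduce the variance of the effect by about 0% when the school-level correlation is low or equal to the within-school one, about 5-7% at 0.6-0.7, and about 10-25% at 0.8-0.9. Single settings go further: 11% at 0.7 when the student's own answer predicts weakly, and more at 0.9 in the linear approximation. The variance ratio of 0.82 at correlation 0.9 equals 1/0.82 = 1.22, or about 22% more schools, but that figure needs the 0.9.

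These sizes rest on assumed correlations, an ICC of 0.02 that is taken as equal at both times, and 120 analysed students in every school. The document gives no basis for choosing within the range. The case for the change is therefore its asymmetry: at low correlation it costs almost nothing (variance ratio at most 1.02 in the settings simulated), and at high correlation the gain is material.

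**What to change.** In {20a}, state that the primary model includes two baseline terms: the student's own baseline 30-day alcohol use, and the school's baseline prevalence of it, taken as the mean over all baseline respondents in the school. Specify the matching pair for each secondary outcome: own baseline value and school mean. If the full analysis plan already does this, one sentence in {20a} saying so is enough.

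The cost is one school-level degree of freedom out of about 68 (70 schools less two arms). It needs no new data, participants or procedures, and the sample size need not change.

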### Interim analyses {21b}

Not applicable. There will not be interim analyses because the data will be analyzed at the end of the trial.

### Methods for additional analyses (e.g., subgroup analyses) {20b}

Subgroup analyses will be performed to explore differences between males and females and between grades (6th and 7th grade). The statistical approach will follow the procedures described above.

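### The subgroup section asks whether the effect differs by sex or grade, but the method it names estimates only the arm effect, not the difference between subgroup effects

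*Protocol article*

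**What the plan says.** Under *Methods for additional analyses {20b}* the protocol article states the aim: "Subgroup analyses will be performed to explore differences between males and females and between grades (6th and 7th grade"). It then fixes the method by reference: "The statistical approach will follow the procedures described above".

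The procedures above are in *Statistical methods for primary and secondary outcomes {20a}*. Odds ratios with 95% confidence intervals "will be calculated as the measure of association between experimental condition (Intervention arm) and behavioral outcome, controlling for baseline outcome variable scores", and for clustering "a multilevel modeling approach will be followed in the analysis of the data". The analysis is by intention to treat.

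No arm-by-sex or arm-by-grade term, and no other comparison of subgroup effects, appears in either section or elsewhere in the article. Nor does the article give a rule for reading subgroup p-values.

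**The concern.** The question and the named method do not match. Whether the programme works differently in boys and girls, or in 6th and 7th grade, is a question about the difference between two arm effects. The method referred to delivers an arm effect. Applied to each subgroup in turn, it gives four odds ratios (two for sex, two for grade), and none of them estimates a difference.

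The risk is a familiar one. When one subgroup's interval excludes 1 and the other's does not, readers tend to conclude that the programme works in one group only. Two estimates of the same true effect often fall on opposite sides of the significance threshold by chance. The article's Discussion looks ahead to wide implementation if the effects are positive, so a spurious pattern of this kind could influence who is offered the programme.

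**Working it through.** **Inputs, all from *Sample size {14}* unless marked**

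- Error rates: "Assuming alpha 0.05 (two-sided), power 0.80".
- Control prevalence: "with a prevalence of regular alcohol use in the control arm of 4.18" per cent, so p1 = 0.0418.
- Effect: "assuming an Absolute Risk Reduction (ARR) of 2% in favor of the intervention group", so p2 = 0.0218.
- Clustering: "30 students per class, and Intraclass Correlation (ICC) of 0.02".
- 4200 students and 35 schools per arm, hence 4200/35 = 120 students per school. This is four classes of 30, in line with the eligibility rule of at least two classes in each grade.
- Assumption (not in the article): each subgroup is half of each school, 60 students, so 2100 per arm.

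**Step 1. Reproduce the plan's own figure.** The two-proportion formula with pooled variance under the null and no continuity correction gives 1208 per arm for individual randomisation. The design effect is 1 + (120 − 1) × 0.02 = 3.38. Then 1208 × 3.38 = 4083, and 4083/120 = 34.03, rounded up to 35 schools, or 35 × 120 = 4200 per arm. The stated size is reproduced, with the school as the cluster.

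**Step 2. Power within one subgroup.**

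- Design effect: 1 + (60 − 1) × 0.02 = 2.18.
- Effective size per arm: 2100/2.18 = 963.3.
- Standard error under the null: √(2 × 0.0318 × 0.9682/963.3) = 0.00800.
- Standard error under the alternative: √((0.0418 × 0.9582 + 0.0218 × 0.9782)/963.3) = 0.00798.
- Expected z: 0.02/0.00798 = 2.51.
- Power: Φ((0.02 − 1.96 × 0.00800)/0.00798) = Φ(0.542) = 0.706.

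**Step 3. Chance that exactly one subgroup is significant when the true effect is the same in both.**

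- Subgroups independent: 2 × 0.706 × 0.294 = 0.415.
- School effect fully shared by the two halves: the correlation between the subgroup estimates is 60 × 0.02/2.18 = 0.55. Both are then significant with probability 0.572 (bivariate normal), so exactly one is significant with probability 2 × (0.706 − 0.572) = 0.268.

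**Step 4. Check by simulation.** This used 20,000 trials, 35 schools per arm, beta-binomial outcomes with ICC 0.02 fully shared within school, and school-level t tests.

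| True state | Exactly one subgroup significant | Direct test of the difference significant |
|---|---|---|
| Same effect in both subgroups | 27.6% | 5.3% |
| No effect in either | 7.6% | 5.0% |

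**Step 5. Power of the direct test.** Take the extreme case in which the whole effect lies in one subgroup.

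- The log ratio of odds ratios is 0.672. The variances of the two subgroup log odds ratios are 0.0746 (with effect) and 0.0518 (without).
- Independent subgroups: SE = √(0.0746 + 0.0518) = 0.356, and power is Φ(0.672/0.356 − 1.96) = 0.47.
- School effects fully shared (correlation 0.55): SE = √(0.0746 + 0.0518 − 2 × 0.55 × √(0.0746 × 0.0518)) = 0.241, and power is about 0.80.

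Smaller differences between subgroups would be detected less often in either case.

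**The case against.** The strongest reply is that the article never says the model is repeated, stratified or fitted separately. A multilevel logistic model with an arm-by-sex product term uses every element of *{20a}*: intention to treat, odds ratios with 95% CI, baseline adjustment and allowance for clustering. The stated aim of exploring differences could be read as pointing to exactly that model. The form of the interaction is often left to the analysis plan, which is not at hand. The analysis is also described as exploratory.

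Much of this stands. An interaction term is not excluded. A reader might infer that the plan commits itself to separate fits, or that conclusions about who benefits will rest on separate subgroup p-values. The article supports neither inference, because it names no stratified fit, no subgroup significance rule and no intention to claim benefit in one group only.

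It does not remove the point. The article does not defer the subgroup method. It names one, and the only quantity that method is said to estimate is the arm effect. An analyst could omit any comparison between subgroups and still comply.

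A second objection concerns the size. The lower figure of 27% assumes that all clustering is a school effect shared equally by both halves. For grade, the two subgroups sit in different classes, and the article gives no class-level or grade-level ICC. That objection is right: for grade, the figure can only be placed somewhere between 27% and 41%.

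**Conclusion.** The point holds in a limited form. The section asks about differences between subgroups, and the method it names includes no estimate or test of those differences. Separate fitting is the natural reading, though not a stated one.

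If the analysis is done by separate fits, and the true effect is the same in both subgroups, about 27% to 41% of trials would show significance in exactly one subgroup, for each factor. A direct test of the difference would err in about 5%. These figures rest on the planned rates of 4.18% and 2.18%, an ICC of 0.02, a 60/60 split in every school, complete data and no gain in precision from baseline adjustment. They describe how often the pattern would arise. They do not show that the investigators would misread it.

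The primary outcome and its analysis involve no subgroup, so the primary conclusion is unaffected. The severity is minor.

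**What to change.** In *Methods for additional analyses {20b}*, say how the difference will be estimated:

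- Add an arm-by-sex term and, in a separate model, an arm-by-grade term to the same baseline-adjusted multilevel model.
- Report each ratio of odds ratios with its 95% CI and interaction p-value.
- Show the within-group odds ratios as descriptive only.
- Label the analysis exploratory, with limited power.

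If a full protocol or analysis plan already specifies this, the article's sentence need only be brought into line with it.

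The cost is a short addition to the text and two extra model fits on data already to be collected. The one drawback is that the interaction test may well miss a real difference, so the confidence interval should carry the interpretation and a non-significant result should not be read as proof of equal effects.
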